### Randomization and allocation

Treatment allocation occurs when the study participant meets the inclusion criteria and signs the informed consent form. The teletherapist will then register the participant into the database, which, in turn, asks if they are ready to be randomized. After the teletherapist enters Yes, the site-specific randomization program displays the participant's group assignment number (placebo versus Chinese medical herb). Site-specific randomization lists will be computer-generated (that is, generated by an individualized basic visual code program) and concealed from the researchers by a senior data manager, who is not involved in the study. This information will remain confidential and is not shared with the study sites, in concordance with the CONSORT guidelines. This trial uses a prospective, randomized, outcome-blinded design, in which all outcome assessments are made by a research assistant blinded to treatment allocation and uninvolved in patient consent and management. The allocation list will be protected by password access files and held by an independent non-investigator. In the event of a clinical emergency, the individual's randomization code and group allocation can be identified.

### Sample size

The sample size calculation is based on the effect size of clinical symptom changes in AECOPD subjects from a previous trial of one of the most commonly used TCM injections [12]. In that study, the mean effective change in clinical symptoms was 97% in the treatment group, compared to 87% in the placebo group (*P *< 0.05). For the proposed study, to achieve a similar difference between the TCM and placebo treatment groups with an 90% power and a two-tailed significance level of 5%, *n*_1 _= *n*_2 _= 1,641.6 × [[]]^2^, the sample size in each group is 145. Considering a 20% drop-out rate over the course of the study, 182 patients will be enrolled in each group, that is, 364 in total. Intention-to-treat analysis will be applied to minimize bias due to drop-outs.

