## Methods and design

### Study design

This clinical trial is multi-centered, randomized, single-blind and placebo-controlled. The design of the study integrates rigorous, contemporary clinical research methodology in accord with principles set out in the Declaration of Helsinki and the Good Clinical Practice guidelines regarding the appropriate use of TCM in clinical practice. Reporting will be guided by the CONSORT statement [10,11]. Subjects are being enrolled at eight hospitals in four sites in China: 1) The First Affiliated Hospital of Henan University of TCM; 2) TCM hospital of Xinjiang Uygur Autonomous Region; 3) Sichuan Province TCM hospital; 4) Jiangsu Province Hospital of TCM; 5) the First Affiliated Hospital of Henan University of Science and Technology; 6) Henan University of Huaihe hospital; 7) The First Affiliated Hospital of Zhengzhou University; and 8) Henan Provincial Chest Hospital. The eight hospitals in China will randomly assign 364 patients with AECOPD in a ratio of 1:1 to the TCM treatment group or matching placebo. Consenting eligible participants will be enrolled for five to eight weeks and required to attend 12 visits in total. The trial has three phases: one to three weeks treatment with either TCM for AECOPD or placebo granules, four weeks treatment with either TCM for AECOPD-RW or placebo granules, and six months follow-up (Figure 1).

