### Symptoms and signs

Symptoms including cough, sputum, dyspnea, fever, acratia, cyanosis, wheezing and respiratory rate, and so on, will be evaluated on days 0 (admission), 4, 7, 14 and 21 during the exacerbation period, each week during the AECOPD-RW period, and in the first, the third and the sixth month during the follow-up period.

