### Statistical analysis

A descriptive statistical analysis will be performed for all study variables. We will calculate the mean, median and standard deviations for quantitative variables, and the absolute and relative frequency for qualitative variables.

We will use SPSS 19.0 (License number: 6f1d84c801f1e6010dc, SPSS Inc. Chicago, Illinois state, United States) to statistically analyze the data. An intention-to-treat analysis will be applied using the Last Observation Carried Forward (LOCF) method for missing data. Analysis of covariance with baseline as covariate will be used to assess differences in treatment outcomes between the two groups at each of these time points. To correct for inflated risk of Type 1 error, multiple comparison procedures suggested by Ludbrook et al. will be used [14]. The use of relief medication during the trial will be investigated for its effect on the outcome measures by using it as a covariate in the statistical analysis. A Data Safety Monitoring Board has been established to assess the progress of the trial, particularly safety endpoints.

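### The 90% power is computed for a comparison of two symptom-response proportions, but the article defines no symptom response and names ANCOVA on means as its test

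*Protocol article*

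**What the plan says.** Protocol article, Sample size: "The sample size calculation is based on the effect size of clinical symptom changes in AECOPD subjects from a previous trial", and there "the mean effective change in clinical symptoms was 97% in the treatment group, compared to 87% in the placebo group". With 90% power and a two-sided 5% level, a formula with the leading constant 1,641.6 gives 145 per group. Then: "Considering a 20% drop-out rate over the course of the study, 182 patients will be enrolled in each group", 364 in total.

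Protocol article, Symptoms and signs: "Symptoms including cough, sputum, dyspnea, fever, acratia, cyanosis, wheezing and respiratory rate, and so on, will be evaluated" on five days of the exacerbation period, weekly in the risk window, and at months 1, 3 and 6. No response category or threshold is given. The Abstract lists clinical symptoms among the primary outcome measures.

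Protocol article, Statistical analysis: "Analysis of covariance with baseline as covariate will be used to assess differences in treatment outcomes between the two groups", at each time point, with a multiple-comparison correction. Qualitative variables appear only under descriptive analysis, as frequencies.

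**The concern.** The planning figures and the analysis concern different kinds of endpoint. The Sample size section treats symptoms as a proportion of patients with an effective response, although its word *mean* blurs this. The other two sections treat them as ratings whose baseline-adjusted means are compared. Nothing in the article links the two: there is no responder definition on one side, and no mean difference or standard deviation on the other.

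The 145 per group and the 90% power are the trial's only planning figures. If they describe a different test from the one reported, a reader cannot use them to judge what symptom effect the trial was designed to detect. This is separate from the question of which outcome is primary. Making symptoms the sole primary outcome would leave the mismatch in place.

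**Working it through.** **Inputs.** From Sample size: 97% and 87%, 90% power, two-sided 5%, constant 1,641.6, 145 per group, 20% drop-out. From Study design: 1:1 allocation. The sum of normal quantiles is 1.960 + 1.282 = 3.242. No SD, symptom score or target mean difference is given anywhere.

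**1. Which formula is it?** One radian is about 57.3 degrees, and 57.3²/2 = 1,641.6. That is the constant of the arcsine formula for two proportions in degrees:

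n = 1,641.6 × [3.242 / (arcsin√p₁ − arcsin√p₂)]²

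The bracket is missing from the text at hand, but the constant is enough to identify the method.

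**2. Does it reproduce 145?** For 97% vs 87% the angles differ by about 11.16 degrees, so n = 1,641.6 × (3.242/11.16)² ≈ 138.5, that is 139. Other two-proportion formulas give:

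| Method | n per group | Power at 145 |
|---|---|---|
| Arcsine | 139 | 91.3% |
| Unpooled variance | 150 | 89.1% |
| Pooled variance | 153 | 88.5% |

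The printed 145 is not matched exactly, but rounding of the two rates could explain the gap: by arcsine, 96.7% vs 86.8% gives 147 and 97.0% vs 87.2% gives 143. Power at 145 is within 2 points of 90% by each method. The drop-out step reproduces: 145/0.8 = 181.25, so 182 per group and 364 in total. As a two-proportion calculation, the section is sound enough.

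**3. What does 145 per group give for the named test?** For a comparison of means at two-sided 5% and 90% power, the detectable standardised difference is

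3.242 × √(2/145) ≈ 0.38.

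Baseline adjustment multiplies this by √(1 − r²), where r is the baseline correlation. The document gives no r. Assumed values of 0.3, 0.5 and 0.7 give 0.36, 0.33 and 0.27. All of these are for one test at 5%; a stricter level from the planned multiplicity correction would raise them.

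**4. Can 97% vs 87% be carried over to means?** Only with assumptions the document does not supply.

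- *As mean percentage improvement.* The constant argues against this reading. If it were right, a 10-point difference would have 90% power at an SD of 10/0.38 ≈ 26.3. On a 0–100% scale a mean of 97 allows an SD of at most √(97×3) = 17.1, and a mean of 87 at most √(87×13) = 33.6. The pooled maximum is √((291+1,131)/2) ≈ 26.7, so power would be at least about 89%.
- *As response rates cut from a normal score.* The difference would be z(0.97) − z(0.87) = 1.881 − 1.126 ≈ 0.754 SD. About 37 per group would suffice, and power at 145 would exceed 99.9%.

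The second reading depends on normality and on an unseen cut-off. Neither gives a power that could be stated for this trial.

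**The case against.** The strongest reply is that a condensed article may leave a response threshold, and a test for a categorical endpoint, to the full protocol or analysis plan. The ANCOVA sentence is also plainly not a full list of tests, since mortality and time to next exacerbation have no natural baseline covariate. This stands in part: one cannot conclude that no comparison of response proportions will ever be made. What remains is that the article commits to one kind of comparison when sizing the trial and names another for the analysis, and nothing in it connects them.

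A reader might also infer that the trial is underpowered for symptoms, because a 10-point mean difference with an SD of 30 or 40 would have power of only 81% or 57%. The documents do not support this. Those SDs have no source in them, the constant points to proportions rather than means, and on a 0–100% scale the SD cannot be that large.

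A third reply is that a null result is read from its confidence interval, so the planning figure matters less. That is fair, and it limits the harm. The figure still tells readers what the trial was built to detect, and here it does so for a different test.

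Lastly, the stated objective is exacerbation frequency, so the sizing might be replaced altogether. That is a separate matter. While the symptom calculation stands, it should match the symptom analysis.

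**Conclusion.** The concern holds as a misalignment, not as an arithmetic error. The two-proportion calculation reproduces its 90% to within 2 points, but that power does not attach to the ANCOVA that the article names for its outcomes. The direction of the discrepancy is unknown. What can be said without further data is that 145 per group detects about 0.38 SD at 90% power before baseline adjustment, and about 0.33 SD at an assumed baseline correlation of 0.5, for a single two-sided 5% test. The conclusion rests on reading 1,641.6 as the arcsine constant and applies to the article as published; an analysis plan that is not shown could add a responder analysis. It is worth correcting because the fix is cheap and these are the trial's only planning figures.

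**What to change.** Keep 364 patients and choose one route.

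(a) Specify a yes/no symptom response at one fixed day from randomisation, stated in this trial's own terms rather than by reference to the cited trial's rule, which the article does not give. Compare the proportions stratified by TCM syndrome, the factor named for stratified randomisation under Interventions. Keep the two-proportion power statement for that test, with 97% and 87% labelled as assumed rates.

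(b) Keep ANCOVA on one total symptom score at one fixed day. Replace the claim of 90% power for 97% vs 87% with the detectable difference for that score: about 0.38 SD before baseline adjustment. Convert it to score units with a blinded pooled SD from patients already recruited (105 at manuscript submission, per Trial status). A restated power, as opposed to a detectable difference, would also need a justified target difference.

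The cost is wording, plus one blinded SD estimate under (b). Neither route needs more patients or spends any alpha. The drawback is that the restated figure may be less favourable than the one now printed.

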### Outcome measurements

#### Primary outcome measure

##### Exacerbations

Frequency, nature and severity of exacerbations of COPD will be evaluated in the first, the third and the sixth month during the follow-up period. If the interval between two events of acute exacerbation is within five days, it can be counted as one acute exacerbation.

Respiratory symptoms are classified as "major" symptoms (dyspnea, sputum purulence, sputum amount) or "minor" symptoms (wheezing, sore throat, cough, and symptoms of a common cold which were nasal congestion/discharge). Exacerbations are defined as the presence for at least two consecutive days of an increase in any two "major" symptoms or an increase in one "major" and one "minor" symptom according to criteria modified from Anthonisen and colleagues [13]. The first of the two consecutive days is taken as the day of onset of exacerbation.

We will also analyze recovery from exacerbation, because in most clinical studies a patient not having an exacerbation for four to six weeks would be considered stable. The time to the onset of the next exacerbation is defined as the number of days from onset of one exacerbation to onset of the next exacerbation [1].

### Symptoms and signs

Symptoms including cough, sputum, dyspnea, fever, acratia, cyanosis, wheezing and respiratory rate, and so on, will be evaluated on days 0 (admission), 4, 7, 14 and 21 during the exacerbation period, each week during the AECOPD-RW period, and in the first, the third and the sixth month during the follow-up period.

### Dyspnea

The modified medical research council dyspnea (MMRC) scale, which was first developed by the British Medical Research Council (MRC), and later revised by the American Thoracic Society (MMRC), will be observed and recorded before treatment, each week during the treatment period, and in the first, the third and the sixth month during the follow-up period.

### Secondary outcome measure

#### Secondary outcome measures include efficacy and safety components

2.1 Quality of life (QoL): QoL assessed by the COPD Assessment Test (CAT) will be observed and recorded on Day 0 (admission), after exacerbation and after AECOPD-RW during the treatment period, and in the first, the third and the sixth month during the follow-up period.

2.2 Lung function: Lung function using spirometry indices of FEV_1_, FVC and FEV1/FVC ratio will be tested and recorded on Day 0 (admission), after exacerbation and after AECOPD-RW during the treatment period, and in the third month during the follow-up period.

2.3 Mortality rate: All-cause mortality will be recorded at the end of the sixth month during the follow-up period.

### Adverse event reporting

Routine calibration and standard operating procedures will be uniformly undertaken at each site. Participants will be advised not to use respiratory medications for several hours prior to their spirometry testing. Two sets of measurements will be taken at each visit, pre-bronchodilator and post-bronchodilator (post 400 μg of inhaled Salbutamol).

Any adverse events will be listed in the trial record and followed up to completion by the trial coordinators and respiratory physicians. Adverse event details will be scored using a six-point scale, 0 = none, 1 = minimal, 2 = mild, 3 = moderate, 4 = severe, and 5 = extremely severe. Participants will be able to report adverse events anytime throughout the trial and will receive advice accordingly. Serious adverse events will be reported to the reviewing HREC and site HRECs within the timeframe specified by the lead HREC.

Throughout the study period trial coordinators will contact the participant's usual treating doctor to record relevant data on presentations and exacerbations.

To assist with outcome documentation and medication compliance, participants will be given a participant diary for the duration of the trial. They will be asked to record trial medication and relief medication usage as well as any new medications they commence during the trial.

Participants may withdraw from the study for any reason at any time without repercussion. They will only be withdrawn by investigators if it is deemed medically unsafe for them to continue. Dropouts will not be replaced.

### Statistical analysis

A descriptive statistical analysis will be performed for all study variables. We will calculate the mean, median and standard deviations for quantitative variables, and the absolute and relative frequency for qualitative variables.

We will use SPSS 19.0 (License number: 6f1d84c801f1e6010dc, SPSS Inc. Chicago, Illinois state, United States) to statistically analyze the data. An intention-to-treat analysis will be applied using the Last Observation Carried Forward (LOCF) method for missing data. Analysis of covariance with baseline as covariate will be used to assess differences in treatment outcomes between the two groups at each of these time points. To correct for inflated risk of Type 1 error, multiple comparison procedures suggested by Ludbrook et al. will be used [14]. The use of relief medication during the trial will be investigated for its effect on the outcome measures by using it as a covariate in the statistical analysis. A Data Safety Monitoring Board has been established to assess the progress of the trial, particularly safety endpoints.

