**Methods/Design:**

A prospective, multi-center, single-blinded, double-dummy and randomized controlled clinical trial is being conducted to test the therapeutic effects of a sequential two stage treatment, which includes eliminating pathogen and strengthening vital qi with syndrome differentiation. A total of 364 patients will be enrolled in this study with 182 in each treatment group (TCM and control). Patients received medication (or control) according to their assigned group. TCM for AECOPD were administered twice daily to patients with AECOPD over 7 to 21 days, followed by TCM for AECOPD-RW over 28 days. All patients were followed for six months. The clinical symptoms, the modified medical research council dyspnea (MMRC) scale and exacerbations were used as the primary outcome measures. Pulmonary function, quality of life and mortality rate were used as secondary outcome measures.

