### Objective

The objective is to determine whether sequentially eliminating pathogens and strengthening vital qi treatment with syndrome differentiation reduces COPD exacerbation frequency.

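### The only stated between-group test, baseline-adjusted ANCOVA with LOCF, does not fit exacerbation frequency, the trial's objective and one of its three primary outcomes

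*Protocol article*

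**What the plan says.** The Objective section asks one question, whether sequential pathogen elimination and "strengthening vital qi treatment with syndrome differentiation reduces COPD exacerbation frequency". The abstract gives three primary outcomes: "The clinical symptoms, the modified medical research council dyspnea (MMRC) scale and exacerbations were used as the primary outcome measures".

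Under Exacerbations, the count belongs to follow-up: "Frequency, nature and severity of exacerbations of COPD will be evaluated in the first, the third and the sixth month during the follow-up period". That section also plans a time-to-event quantity: "The time to the onset of the next exacerbation is defined as the number of days from onset of one exacerbation to onset", where the second onset is that of the following event. Among the secondary outcomes, "All-cause mortality will be recorded at the end of the sixth month during the follow-up period".

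The Statistical analysis section names a single between-group method: "Analysis of covariance with baseline as covariate will be used to assess differences in treatment outcomes between the two groups". The comparison is to be made at every assessment time. It adds: "An intention-to-treat analysis will be applied using the Last Observation Carried Forward (LOCF) method for missing data". Neither sentence is limited to a type of outcome. The article names no count, survival or binary method.

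**The concern.** A baseline-adjusted ANCOVA needs a pre-treatment value of the outcome. Symptoms are scored on day 0 and MMRC before treatment. Exacerbations have no counterpart: the article describes neither a pre-treatment count nor an exacerbation history. The stated model therefore cannot be run as written on the outcome that the objective names.

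The second difficulty is time at risk. The Sample size section expects 20% of patients to drop out, and the article says that they are not replaced, so follow-up will vary between patients. A comparison of mean counts has no place for that, and LOCF hides it: a patient lost at month 1 with no event enters month 6 as event-free. If one arm loses more patients, it shows fewer exacerbations for that reason alone, and the main question of the trial could get a distorted answer.

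**Working it through.** **Which outcomes the stated model fits**

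| Outcome | Role | Pre-treatment value in the article |
|---|---|---|
| Symptoms | primary | yes, day 0 |
| MMRC | primary | yes, before treatment |
| Exacerbation frequency | primary, and the objective | none |
| CAT, spirometry | secondary | yes, day 0 |
| Time to next exacerbation | listed under Exacerbations | none possible; censored if no further event |
| Mortality | secondary | none |

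**The plan's own figures.** The Sample size section gives 145 per group and 20% dropout: 145 / (1 − 0.20) = 181.25, rounded up to 182, or 364 in total. This reproduces. The 145 rests on a symptom response of 97% against 87%, so the article supplies no exacerbation rate, dispersion or rate ratio. Those inputs are assumed below.

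**Bias when exposure is ignored.** Assume a constant event rate and dropout times spread evenly over follow-up. Mean exposure, as a fraction of full follow-up, is then 1 − d/2 for dropout proportion d. With no true effect, the ratio of mean counts equals the ratio of exposures.

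- 20% against 20%: 0.90 / 0.90 = 1.000
- 25% against 15%: 0.875 / 0.925 = 0.946
- 30% against 10%: 0.85 / 0.95 = 0.895

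The arm that loses more patients looks better.

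**Simulation.** There were 182 patients per arm and 4,000 runs per setting. Counts were negative binomial with mean m per six months and variance m + k·m². The last cumulative count was carried forward. Linear means a two-sample comparison of mean counts, the nearest runnable form of ANCOVA when there is no baseline. Rate means the log ratio of events per unit of follow-up with a robust variance, standing in for the offset model. Power is for a true rate ratio of 0.7. In the unequal setting the control arm loses 30% and the TCM arm 10%.

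| m, k | Dropout | Type I error, linear | Type I error, rate | Power, linear | Power, rate |
|---|---|---|---|---|---|
| 0.5, 0.5 | 20 / 20 | 5.0% | 5.1% | 45.7% | 47.5% |
| 0.5, 1.0 | 20 / 20 | 4.6% | 5.0% | 40.3% | 42.1% |
| 1.0, 0.5 | 20 / 20 | 4.9% | 4.9% | 67.9% | 70.1% |
| 1.0, 1.0 | 20 / 20 | 4.6% | 5.1% | 56.0% | 58.3% |
| 0.5, 0.5 | 30 / 10 | 8.9% | 5.2% | 25.4% | 48.9% |
| 0.5, 1.0 | 30 / 10 | 8.8% | 5.2% | 21.4% | 42.2% |
| 1.0, 0.5 | 30 / 10 | 12.5% | 5.1% | 38.8% | 70.2% |
| 1.0, 1.0 | 30 / 10 | 10.9% | 5.0% | 31.1% | 60.4% |

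The Monte Carlo standard error at 5% is √(0.05 × 0.95 / 4000) = 0.34 percentage points. The equal-dropout type I errors are therefore indistinguishable from 5%.

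**Time to next exacerbation.** At assumed means of 0.4 to 1.2 events per six months, the share of patients with no event runs from exp(−1.2) = 0.30 (Poisson) to 1 / (1 + 0.4) = 0.71 (negative binomial, k = 1). For them the interval is censored.

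**The case against.** The strongest reply is that the ANCOVA sentence speaks of group differences at time points. It can be read as meant for the repeatedly measured outcomes that have a baseline, with the rest left to a fuller plan. For time to next exacerbation and mortality this largely stands. The article does not say that ANCOVA will be used for them, and a condensed article may leave the method elsewhere. It does not clear exacerbation frequency, which is a primary outcome, is the objective, and is itself evaluated at set time points. The one stated method is the one a reader would apply to it.

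The second reply is that the harm depends on assumptions. This also stands in part. The plan gives one dropout figure, with no difference between arms, and under equal dropout the loss is small. A count is not ruled out of a comparison of means at this sample size merely because it is not normally distributed. A difference in mean counts would also address the objective, which does not itself require a rate ratio.

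A reader might infer three stronger points that the documents do not support:

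- **That ANCOVA is prescribed for every outcome, or that the whole primary comparison is invalid.** The text does not say every, and symptoms and MMRC have the baseline that the model needs.
- **That time to next exacerbation will be compared among relapsers only.** The article defines an interval and names no estimator. Days are a continuous measure; the difficulty is censoring.
- **That an onset-to-onset clock biases the result by including time before randomisation.** The article does not say that the index event starts the clock. If it does, that time should balance between arms on average.

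**Conclusion.** The point holds for exacerbation frequency. The stated test lacks the covariate it requires and, combined with LOCF, ignores time at risk. This is a method fixed badly, not a detail left out.

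The size depends on dropout. With 20% in both arms, type I error is 4.6% to 5.0% and power is 40% to 68%, against 42% to 70% for a rate analysis. With an assumed 30% against 10%, the spurious count ratio is about 0.895, type I error is 8.8% to 12.5%, and power for a rate ratio of 0.7 is 21% to 39% against 42% to 70% when the control arm loses more.

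These figures assume event rates and dispersions that the article does not give, a constant rate, and dropout unrelated to a patient's risk. If events cluster early in follow-up, the bias would be smaller. The documents do not show that dropout will differ between arms, so the result is exposed to this bias rather than known to be biased.

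For time to next exacerbation and mortality, the point is only a request to clarify.

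**What to change.** **Main change, in the Statistical analysis section:**

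- Analyse the number of exacerbations with a negative binomial (or overdispersed Poisson) model, with log follow-up time at risk as offset.
- State when time at risk starts and ends. If it starts with the follow-up period, patients who leave during treatment contribute no time, so say how they are handled.
- Do not apply LOCF to counts.
- Adjust for the TCM syndrome stratum used in randomisation.
- Report a rate ratio with 95% CI.
- Limit baseline-adjusted ANCOVA to outcomes with a pre-treatment value: symptoms, MMRC, CAT and spirometry.

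**Secondary clarifications:**

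- Analyse time to next exacerbation with a censored method (Kaplan-Meier and Cox) from a stated post-randomisation origin. Patients are randomised during an exacerbation, so a rule must separate a new event from the index one.
- Analyse mortality with a survival method or an exact test.

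**Cost.** The main change is analysis wording and uses standard software. It needs no new data; exacerbation history for the previous year would be an optional covariate and is not required. The article reports 105 of 364 patients recruited, so the wording can be settled before unblinding. The offset model still assumes that dropout is unrelated to exacerbation risk, which should be stated.

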**Discussion:**

It is hypothesized that sequentially eliminating pathogens and strengthening vital qi treatments with syndrome differentiation will have beneficial effects on reducing the frequency and duration of acute exacerbation, relieving symptoms and improving quality of life for COPD patients.

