### Interventions

Eligible patients will be randomized to one of the two arms: placebo or Chinese medical herb (11.65 g twice daily). Three TCM formulas for exacerbation will be administered orally for 7 to 21 days: sanhanhuayinfang (*Ephedra, Rumulus Ginnamomi, Rhizoma Zingiberis*, and so on), qingrehuatanfang (*Mongolian snakegourd fruit, Rhizoma Pinelliae, Bulbus Fritillariae Cirrhosae *and so on), zaoshihuatanfang (*Prepared Pinellia Tuber, Officinal Magnolia Bark, Tangerine Peel *and so on). There are also three TCM formulas for AECOPD-RW that will be administered orally for four weeks; they are: bufeijianpifang (*Codonopsis, Astragalus root, Largehead Atractylodes Rhizome, Perilla Fruit, Mangnolia officinalis*, and so on), bufeiyishenfang (*Ginseng, Astragalus root, medlar *and so on), yiqizishenfang (*Ginseng, solomonseal, Rehmannia Glutinosa *and so on). All drugs were made into granules by Jiangyin Tianjiang Pharmaceutical Co., Ltd. Jiangyin city, Jiangsu province, China). In this study, the subjects and statisticians will be blinded to treatment assignment. In this respect, the trial is single-blind. Randomization of subjects will occur centrally using a random number generator and will be stratified by syndrome differentiation of TCM. (Syndrome, as related to illnesses in Western medicine, is composed of a set of signs and/or symptoms classified by Traditional Chinese Medicine practitioners. TCM Syndrome differentiation is based on symptoms and helps to identify a subset of disease). Patients will visit the doctor at one-, three- and six-month follow-ups.

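### Relief medication taken during the trial is planned as a covariate, and the plan does not say that the treatment effect is read only from the baseline-adjusted model

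*Protocol article*

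**What the plan says.** Only the protocol article is available. Its Statistical analysis section makes three statements that bear on this point.

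- The group comparison: "Analysis of covariance with baseline as covariate will be used to assess differences in treatment outcomes between the two groups".
- The analysis principle: "An intention-to-treat analysis will be applied using the Last Observation Carried Forward (LOCF) method for missing data".
- After the multiplicity sentence, the relief-medication plan: "The use of relief medication during the trial will be investigated for its effect on the outcome measures by using it as a covariate". The sentence ends by placing this in the statistical analysis, without naming an outcome, a model or a rank.

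The Adverse event reporting section shows when relief use is measured. Participants keep a diary throughout the trial: "They will be asked to record trial medication and relief medication usage as well as any new medications they commence during the trial".

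The abstract supplies the link to the outcomes. On what is measured: "The clinical symptoms, the modified medical research council dyspnea (MMRC) scale and exacerbations were used as the primary outcome measures". On what TCM is expected to do, it names "reducing the frequency and duration of acute exacerbation, relieving symptoms and improving quality of life for COPD patients".

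**The concern.** Relief medication recorded in the diary is a post-randomisation variable. Patients take it because of breathlessness, wheeze and cough, which are also scored as outcomes. This causes two problems once it enters a model that yields a treatment coefficient.

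1. If TCM relieves symptoms as hypothesised, patients will tend to need less relief medication. Holding relief use constant then removes the part of the benefit that runs through it or is marked by it.
2. Relief use and symptom scores share an unmeasured cause, the patient's severity. If treatment shifts relief use, conditioning on it makes the arms differ in severity at any given level of use. A difference can then appear where there is none.

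In either case the coefficient is no longer the randomised comparison that the intention-to-treat statement promises. Two models without a stated order also leave room to choose between them once the results are known.

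**Working it through.** The plan gives no figure to reproduce. It states no relief-use rate, SD or correlation, so every input below except the group size is an assumption.

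**Inputs**
- n = 182 per arm (Sample size section).
- Outcome, relief use and baseline score each have within-arm variance 1. Lower outcome scores are better.
- Severity loads l = 0.6 on both outcome and relief use, and λ on the baseline score. λ = 0 is an uninformative baseline; 0.6 to 0.9 is an informative one.
- TCM lowers relief use by d = 0.4 SD.
- The true effect is -0.30 SD, or zero.
- Relief use has no direct effect on the outcome, so this setting shows the shared-cause bias alone.

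**Formulas**
- Variance of outcome or relief use given baseline: v = 1 − l²λ²
- Slope of outcome on relief use given baseline: b = l²(1 − λ²)/v
- Relief-adjusted estimate = true effect + d·b
- Standard error, baseline only: √(2v/n)
- Standard error, relief-adjusted: √[(2/n)·v(1 − b²)·(1 + d²/(4v))]
- Power ≈ Φ(|estimate|/SE − 1.96). False rejection uses d·b in place of the estimate and adds the opposite tail.

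**Worked case, λ = 0.6**
- v = 1 − 0.36 × 0.36 = 0.8704
- b = 0.36 × 0.64/0.8704 = 0.265
- d·b = 0.4 × 0.265 = 0.106, so −0.30 becomes −0.194
- Baseline-only SE = √(2 × 0.8704/182) = 0.0978; power = Φ(3.07 − 1.96) = 87%
- Adjusted SE = √(0.01099 × 0.8094 × 1.046) = 0.0965; power = Φ(2.01 − 1.96) = 52%
- Under the null, 0.106/0.0965 = 1.10, so rejection is about 20%

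| Baseline loading λ | v | b | Adjusted estimate (true −0.30) | Power, baseline only | Power, adjusted | Rejection under null, adjusted |
|---|---|---|---|---|---|---|
| 0 | 1.000 | 0.360 | −0.156 | 82% | 35% | 30% |
| 0.6 | 0.870 | 0.265 | −0.194 | 87% | 52% | 20% |
| 0.9 | 0.708 | 0.097 | −0.261 | 93% | 83% | 7% |

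Simulation agrees to within about 3 points. For λ from 0.6 to 0.9 it gave estimates of −0.19 to −0.26, power of 84–91% falling to 50–81%, and null rejection of 19% to 8%. With an uninformative baseline it gave −0.15, 33% and 30%.

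**Sensitivity to d.** The bias is proportional to d. At d = 0.2 it halves: the shift is 0.053 for λ = 0.6 and 0.019 for λ = 0.9, giving estimates of about −0.25 and −0.28. At d = 0 the shift is zero. If relief use were higher under TCM, the shift would change sign.

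**Mediation.** A separate simulation with 145 per arm and baseline in both models sent half of a true −0.40 SD effect through relief use. The baseline-only model returned −0.40 with 88% power. Adding relief use returned −0.20 with 38% power.

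**The case against.** The strongest reply is that the group comparison is already fixed as an analysis of covariance in which only baseline is named as covariate. The relief-medication sentence comes later and has a different stated aim: the effect of relief medication on the outcomes, not the effect of treatment. It can fairly be read as a supplementary model, and a condensed article may leave its rank to the full protocol or SAP. This much stands. A reader might infer that the main efficacy model itself contains relief use and that the randomised comparison is lost. The text does not establish that.

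What does not stand is that the wording is therefore harmless. The article itself commits to the covariate, gives it no exploratory label, and does not reserve the treatment effect for the baseline-only model. Even as a supplement, its treatment coefficient would not be an intention-to-treat effect.

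Two points on size also stand. A reader might infer that the effect would be halved and that about 30% of null trials would reject. Those figures need an uninformative baseline, whereas the plan adjusts for baseline, which should carry some of the severity. And the null scenario, in which TCM cuts relief use but leaves symptoms unchanged, is somewhat strained when participants are blinded: "In this study, the subjects and statisticians will be blinded to treatment assignment". Treating clinicians are not in that statement, however, so a difference in relief use for other reasons cannot be ruled out.

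**Conclusion.** The concern holds in a limited form. The plan names a post-randomisation covariate that its own hypothesis expects treatment to change, and does not say that treatment effects will be read only from the baseline-adjusted model. Any treatment coefficient taken from a relief-adjusted model would be biased if treatment changes relief use, and unbiased in these scenarios if it does not.

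With the planned baseline covariate and a 0.4 SD reduction in relief use, the illustration loses roughly 0.04 to 0.11 SD of a 0.30 SD effect and raises false rejection above 5%. The direction follows from the setting; the size depends on assumed values that the document cannot confirm. A reader might also infer that the adjustment would produce a false claim of benefit. Here it does the reverse: lower relief use under TCM pushes the estimate against TCM.

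**What to change.** In the Statistical analysis section:

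1. State that treatment effects on all efficacy outcomes are estimated from the analysis of covariance with baseline covariates only, regardless of relief-medication use, and remove during-trial relief medication from those models.
2. Report relief-medication use by arm as an outcome in its own right, from the diary.
3. If any model with relief use as a covariate is kept, label it exploratory and draw no conclusion about the treatment effect from it.
4. If background therapy is the concern, adjust only for medication recorded at Day 0. The article does not say that this is recorded, so that should be confirmed first.

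The cost of items 1 to 3 is a few sentences. The diary already collects relief use, and neither the sample size nor the significance level changes. The Trial status section reports 105 of the planned 364 patients recruited at submission, so the wording could be settled before recruitment ended.
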